#### Exploratory outcome

Lifestyle/behavior, such as near work time and outdoor time, are potential confounding factors for myopia development. Eye care instruction may impact near work time and outdoor time. We will evaluate the changes in these factors over the study period and include them as the exploratory outcomes. Besides, time to myopia onset and changes in mean subfoveal choroidal thickness over the study period will also be exploratory outcomes.

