### Questionnaire survey and compliance assessment

To collect information on potential myopia-related risk factors, the parent-administered questionnaire and eye examinations for all participants at baseline and 9- and 18-month follow-up visits will be conducted. This questionnaire comprises four sections and 16 questions regarding demographic data, parental myopia, medical information, and out-of-school behaviors such as time spent on near work, outdoor activities, sleeping and after-school care service or tutorial programs. These questions are closed-ended and have responses of yes/no options or a list of ordered choices. The respondents were asked to check the choice they felt was the most proper. Table 1 summarizes the survey questions in the questionnaire.

**Table 1 pone.0312935.t001:** Survey questions and responses in the questionnaire.

Caregiver’s information
• Your relationship with the child: □mother, □father, □paternal grandparent, □maternal grandparent, □others______ • Age • Gender • Occupation
• Education level: ➢Child’s father: □primary school, □junior high school, □senior high school/vocational school, □junior college or university, □graduate school or above ➢Child’s mother: □primary school, □junior high school, □senior high school/vocational school, □junior college or university, □graduate school or above • Do the parents have myopia? □no_ none has myopia, □yes_ only father has myopia, □yes_ only mother has myopia, □yes_ both have myopia

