**Attendance of after-school activity (after entering elementary school)**
• Does your child attend after-school activity after entering elementary school? □yes, □no, □not sure ➢If yes, what kind of after-school activity? □on-campus care service/club activity, □off-campus care service, □off-campus tutoring program/cram school, □off-campus compound (care and tutoring) program ➢If yes, how much time a week dose your child spend on after-school activity? □< 5 hours, □≥ 5 hours but < 10 hours, □≥ 10 hours ➢If yes, how many days a week does your child attend on after-school activity? □1 day, □2 days, □3 days, □4 days, □5 days, □6 days, □7 days ➢If yes, how long has your child attended after-school activity? □< 1 semester, □≥ 1 but < 2 semesters, □≥ 2 but < 3 semesters, □≥ 3 semesters

An unpublished study has been conducted among 40 six- to seven-year-old children (22 males and 18 females) and their parents to evaluate the concurrent validity (the agreement between children and parents) and test-retest reliability (parents’ reproducibility estimates) of the questionnaire survey described above. For lifestyle, near work, outdoor activity, attendance of after-school care/tutoring activity, the five-day test-retest reliability was examined using McNemar’s tests (all P > 0.05), and the measure agreement between children and their parents was examined using Cohen’s kappa coefficient (0.68–0.81), which provide the evidence of adequate reliability and validity of this questionnaire.

In addition to the questionnaire, we will give each participant’s parents or caregivers a diary booklet and urge them to record school attendance during the school day and amount of after-school near work activity and outdoor activity. In the treatment groups, atropine eyedrop use or DIMS spectacles wear will also be recorded in the diary daily. Treatment compliance and adherence level will be assessed based on the number of days with atropine use/DIMS spectacles worn as recorded in the dairy. Participants will be considered to have good treatment compliance if the number of days with treatment adherence is more than 80% of the total days that the participants stay in this trial.

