### Statistical analysis

The database of examination parameters and questionnaire items of this study will be constructed with Microsoft Excel software (Redmond, WA, USA). Only the data from the eye with less SE (more myopic or less hyperopic) in each child will be used for identifying refractive status and ocular parameter analysis. Continuous variables will be expressed as mean (SD). Categorical variables will be expressed as frequency and percentage. The independent Student’s t-test, ANOVA, or Pearson’s chi-square test will be adopted to compare the differences between groups in terms of refractive error, demographic characteristics, and questionnaire items. Repeated measures ANOVAs will be used to test the interaction effect of time and treatment for the repeated measures during the follow-up examinations. Statistical analysis will be carried out using IBM SPSS Statistics 26 (IBM Corp., Armonk, N.Y., USA). All p values < 0.05 are considered statistically significant.

For the analysis of the primary outcome, the 1.5-year myopic shift of SE is calculated as the difference in SE between visits at baseline and at Month 18. The changes in SE over the 1.5-year follow-up period will be compared using ANOVA. The post hoc test will be carried out with Bonferroni correction to minimize the potential type I error due to multiple comparisons. The efficacy of myopic shift retardation of the therapeutic intervention is determined by dividing the difference in myopic shift between the treatment group and the control group with the myopic shift in the control group. The intention-to-treat analysis will be adopted to address the issue of loss to follow-up. The missing data in the repeated measures analysis will be dealt with generalized estimating equations (GEE). With one within-subject factor (time), one between-subject factor (treatment assignment) and their interactions, GEE will be employed to determine the treatment effect on the primary outcomes adjusted for some confounding factors, including age, gender, baseline SE, number of myopic parents, time spent on near works and outdoor activities.

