The secondary outcomes include the proportion of incident myopia, the proportion of fast myopic shift of SE, and the changes in mean axial length over the 1.5-year follow-up period. The analyses on the secondary outcomes will also be conducted with intent-to-treat principles. Using exact unconditional methods based on the Farrington-Manning score statistic, we will calculate the difference in the cumulative incidence of myopia among groups of different treatment assignment. As a binary outcome, the proportion of fast myopic shift of SE will be analyzed with Pearson’s chi-square test to compare the difference among groups. In addition, time-dependent Cox regression will be adopted to control the time-varying covariate in the analysis of the incidence of myopia and fast myopic shift of SE. Just like the analysis of myopic shift of SE, we will use ANOVA and Bonferroni correction to compare the mean change of axial length in each group. GEE will also be adapted to the treatment effect on this secondary outcome with the adjustment of the abovementioned confounding factors.

The exploratory outcomes include time to myopia onset, the changes in mean subfoveal choroidal thickness and amounts of near work/outdoor activities over the study period. In the analysis of time to myopia onset, we will assess survival analysis using a Kaplan–Meier method, with the significance based on the log-rank test. As a continuous variable, subfoveal choroidal thickness will be assessed with GEE to compare the changes among the three groups. The differences in the questionnaire items among the three groups will be estimated with ANOVA test.

The interval between the baseline visit and the last follow-up visit before school entrance is defined as “preschool stage”. The interval between the last follow-up visit before school entrance and the final visit is defined as “elementary school stage”. It is estimated that there will be nine months in both stages. The changes in SE and axial length in each stage are calculated as the difference in SE and axial length between the first and the last visits in the stage. We will use a paired t-test to compare the differences in mean change of SE and axial length between preschool and elementary school stages in each group.

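### The adjusted models for treatment effect include near-work and outdoor time without restricting them to baseline, although the protocol treats changes in both as outcomes; if follow-up values enter, the adjusted effect can be biased

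*Protocol article*

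**What the plan says.** The Statistical analysis section compares the Month 18 change in SE by ANOVA with Bonferroni post hoc tests. It then specifies a GEE model with time, treatment and their interaction to determine the treatment effect on the primary outcome, "adjusted for some confounding factors, including age, gender, baseline SE, number of myopic parents, time spent on near works and outdoor activities". The next paragraph applies the same adjustment to axial length. For incident myopia and fast myopic shift it adds that "time-dependent Cox regression will be adopted to control the time-varying covariate in the analysis of the incidence of myopia", without naming that covariate.

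The Exploratory outcome section gives the same two behaviours three roles:
- Confounders: "Lifestyle/behavior, such as near work time and outdoor time, are potential confounding factors for myopia development".
- Variables open to influence during the trial: "Eye care instruction may impact near work time and outdoor time".
- Outcomes: "We will evaluate the changes in these factors over the study period and include them as the exploratory outcomes".

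The Statistical analysis section repeats the last role, listing among the exploratory outcomes "the changes in mean subfoveal choroidal thickness and amounts of near work/outdoor activities over the study period".

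On timing, the section on the questionnaire survey and compliance says that the questionnaire and eye examinations "at baseline and 9- and 18-month follow-up visits will be conducted". The diary described after Table 1 also records the "amount of after-school near work activity and outdoor activity" while the child is in the trial.

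**The concern.** A variable measured after randomisation cannot confound the comparison of randomised arms. If treatment changes it, it lies on the path from assignment to outcome. Conditioning on it removes the part of the effect that runs through it. If it also shares unmeasured causes with refractive change, conditioning on it creates an association between arm and those causes.

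The protocol calls these variables confounders, yet expects that they may change during the trial and analyses that change as an outcome. Its adjustment set does not exclude follow-up values.

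At stake is the meaning of the adjusted estimate. The GEE is the only adjusted model given for the primary outcome. It is also the method named for missing data in the repeated-measures analysis, in a trial that expects 25% dropout. If it conditions on behaviour after assignment, its treatment coefficient does not answer the intention-to-treat question. Leaving the time point open also allows a choice between models once the data are seen.

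**Working it through.** The plan states no figure on this point, so the first check is of the text.

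**1. Which values enter?** The GEE list names age, gender, baseline SE, number of myopic parents, near-work time and outdoor time. The last two carry no time point. They are available at baseline, months 9 and 18, and by diary. Both baseline and follow-up values fit the wording.

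**2. Could behaviour differ by arm?** The one influence the protocol names, instruction, goes to every arm. The document nevertheless contains arm-specific routes:
- No placebo or sham is described for the usual-care control, so families will know their arm.
- Part-time DIMS wear is tied to near work (DIMS spectacle lenses section).
- Photophobia and near blur are expected with atropine (Adverse event section), and parental concern about light outdoors is foreseen (atropine section).
- Outdoor advice is given at each visit, and only the treatment groups have a week-2 visit.

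None of these is quantified.

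**3. What would follow?** An illustrative simulation used two arms of 58, 1,500 runs per scenario and a direct treatment effect of 0.17 D. That is the planning atropine–control difference: 0.55 − 0.38 = 0.17 D at one year. Everything else is assumed:
- a: shift in follow-up behaviour caused by treatment, 0, 0.2 or 0.5 SD.
- g: effect of behaviour on SE change, 0.05, 0.10 or 0.15 D per SD.
- An unmeasured common cause, absent or present. When present, it moves behaviour by 0.5 SD and SE change by 0.15 D per SD of itself.

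The true total effect is 0.17 + a × g. Within-arm behaviour has variance 1, so adjusting for its follow-up value should give 0.17 − a × h. Here h = 0 without the common cause and 0.5 × 0.15 = 0.075 with it. The shortfall is a × (g + h), which is zero when a = 0.

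| a (SD) | g (D per SD) | Common cause | True total (D) | Baseline-adjusted (D) | Follow-up-adjusted (D) |
|---|---|---|---|---|---|
| 0 | 0.10 | no | 0.170 | 0.173 | 0.174 |
| 0 | 0.10 | yes | 0.170 | 0.172 | 0.172 |
| 0.2 | 0.10 | no | 0.190 | 0.190 | 0.171 |
| 0.2 | 0.10 | yes | 0.190 | 0.193 | 0.159 |
| 0.5 | 0.10 | no | 0.220 | 0.223 | 0.173 |
| 0.5 | 0.10 | yes | 0.220 | 0.219 | 0.132 |
| 0.5 | 0.15 | no | 0.245 | 0.245 | 0.169 |
| 0.5 | 0.15 | yes | 0.245 | 0.247 | 0.134 |

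The formula agrees. For a = 0.5, g = 0.10 with the common cause, the shortfall is 0.5 × (0.10 + 0.075) = 0.0875, and 0.220 − 0.0875 = 0.1325 against 0.132 simulated. In the largest case the shortfall is 0.245 − 0.134 = 0.111 D. With a = 0.2 and no common cause it is 0.2 × 0.05 = 0.01 to 0.2 × 0.15 = 0.03 D.

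These runs assume that treatment shifts behaviour in the protective direction. A shift the other way, such as less outdoor time because of glare, reverses the sign of the shortfall. The direction is therefore not fixed either.

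**The case against.** A reader might infer that the adjusted effects are biased as planned. The text does not establish that. No time point is given, and the absence of the word baseline proves little, since age and number of myopic parents lack it too. Baseline behaviour is collected, and using it produced no bias in any scenario. Even follow-up values do no harm in this model unless treatment shifts behaviour, and the advice the protocol names is common to all arms.

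A reader might also infer that the Cox model adjusts for near-work or outdoor time. The covariate is unnamed and could be something else, such as school entry. The Cox model is also additional to the Farrington-Manning comparison of incident myopia and the chi-square test of fast shift.

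Nor does the plan as a whole abandon intention to treat. The ANOVA of the Month 18 change, on which the trial is sized, is stated without covariates, and axial length has its own ANOVA.

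Finally, a percentage is tempting. Half a questionnaire category at 0.05–0.15 D per category gives 0.025–0.075 D. That is 15–44% of 0.17 D, or 7–20% of the DIMS–control difference of 0.55 − 0.17 = 0.38 D. Neither input is in the documents. With SD 0.6 and 58 per arm, the standard error of a difference is 0.6 × √(2/58) ≈ 0.11 D, so such a shift is below one standard error.

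All of this limits the claim. What remains is that the document states an adjustment set, justifies it as control of confounding, and leaves it open to variables it elsewhere treats as outcomes. That goes beyond detail properly left to an analysis plan.

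**Conclusion.** The point holds in conditional form. The GEE for SE, and through it the GEE for axial length, adjusts for near-work and outdoor time not restricted to baseline, while changes in the same variables are exploratory outcomes that the protocol says instruction may alter. If follow-up values enter and treatment shifts behaviour differently by arm, the adjusted estimate can be biased for the effect of assignment. If baseline values enter, or treatment does not shift behaviour, it is not.

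The size cannot be derived from the documents. The illustrated range, zero to about 0.11 D, rests wholly on the assumed behaviour shift, its effect on SE and the common cause. It shows only that the distortion need not be negligible beside a planning difference of 0.17 D. For the Cox model, the finding is limited to the covariate being unnamed.

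**What to change.** In the primary-outcome paragraph of the Statistical analysis section, replace the unqualified near-work and outdoor terms with baseline (pre-randomisation) near-work and outdoor time, or drop them. Keep age, gender, baseline SE and number of myopic parents. The axial-length model refers back to this list, so it needs no separate edit.

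In the secondary-outcome paragraph, name the time-varying covariate of the Cox model. If it is follow-up near-work or outdoor time, remove it from the model for the treatment effect.

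Keep follow-up behaviour as an exploratory outcome, and label any model that conditions on it as exploratory or mediation analysis.

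The cost is a sentence or two. The baseline questionnaire is already scheduled, and sample size and visits do not change. The wording should be settled before outcome data are examined.

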## Introduction

Childhood myopia has been a significant public health concern in East Asia for decades. In Taiwan, the prevalence of myopia surged around the school entry age. Myopia has been found in 9.0% - 10.7% of preschoolers aged 5–6 years, and this rate increased to 19.6% - 19.8% among schoolchildren aged seven years [1–3]. It has been reported that juvenile-onset myopia is associated with rapid progression to high myopia in adulthood [4]. High myopia and its complications may pressure the medical care infrastructure and health insurance system significantly. Therefore, it is imperative to adopt strategies to reduce high myopia by delaying the onset of myopia and myopic shift of refractive state among young children at high risk of developing manifest myopia.

The concept of premyopia, defined as a refractive state of an eye of > -0.50 diopters (D) and ≤ 0.75 D in children with other risk factors for myopia, was proposed by the International Myopia Institute in 2019 for myopia prevention [5,6]. It has been reported that mild hyperopia (> +0.5D to ≤ +2.0D), rather than emmetropia, is the typical outcome of refractive development in children [7]. Our previous study revealed that premyopia was the most common refractive status (52%) in Taiwanese preschoolers [8]. Like myopia, premyopia at preschool age was also associated with environmental factors, such as spending more time on screen-based digital devices and less time on outdoor activities [8]. Several longitudinal studies have demonstrated that the single strongest predictor for myopia onset among nonmyopic children is the baseline status of refractive error [9,10]. Young children with premyopia should be the target population for myopia prevention strategies, especially in the post-COVID-19 era. The COVID-19 pandemic has led to changes in children’s learning patterns and lifestyles, causing an increase in myopia prevalence [11–13].

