### Randomization

The eligible participants will be classified into eight strata based on three factors: baseline cycloplegic SE (+0.50 D to < +1.00 D vs >-0.50 D to +0.25 D), gender (male vs female), and parental myopia (one vs two parents). All these factors are associated with myopia development. At the baseline visits, participants in each stratum will be randomly assigned in a 1:1:1 ratio to one of three groups: treatment group 1 (DIMS spectacle lenses), treatment group 2 (0.01% atropine eyedrops), or the control group (usual care). Random allocation will be conducted using a random sequence generated in Excel, with block randomization applied using a block size of 3.

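### The tests named for incident myopia and time to onset ignore baseline SE and the randomisation strata, which makes them mildly conservative and costs modest power

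*Protocol article*

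**What the plan says.** All places are in the protocol article.

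- **Incident myopia (secondary), Statistical analysis:** "Using exact unconditional methods based on the Farrington-Manning score statistic, we will calculate the difference in the cumulative incidence of myopia among groups". No strata or baseline covariates are named.
- **Time to myopia onset (exploratory), same section:** "we will assess survival analysis using a Kaplan–Meier method, with the significance based on the log-rank test". No strata are named.
- **Cox model, same section:** "time-dependent Cox regression will be adopted to control the time-varying covariate in the analysis of the incidence of myopia". The covariates are not listed.
- **Randomization:** "The eligible participants will be classified into eight strata based on three factors: baseline cycloplegic SE", gender and number of myopic parents, allocated 1:1:1 in blocks of 3. The section adds that all three factors are linked to myopia development.
- **Introduction:** several longitudinal studies are said to show that "the single strongest predictor for myopia onset among nonmyopic children is the baseline status of refractive error".
- **SE change, Statistical analysis:** the GEE is "adjusted for some confounding factors, including age, gender, baseline SE, number of myopic parents", among other factors. For axial length, "GEE will also be adapted to the treatment effect on this secondary outcome with the adjustment of the abovementioned confounding factors".

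The adjustment is thus written out for the two continuous outcomes and not carried over to the two myopia-onset tests.

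**The concern.** The event is SE at or below -0.5 D (Definition of outcome). Children enter anywhere between just above -0.50 D and just below +1.00 D (Participants' recruitment and eligibility). Part of each child's risk is therefore set by distance from the limit at entry.

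Stratified blocks balance the arms on the two-level SE factor. A test that ignores the factor still counts the between-stratum variation as chance, although the allocation has removed it from the comparison. The standard error is then too large, the true error rate falls below the nominal 5%, and power is lost.

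At stake is the ability to show an effect on myopia onset. The sample size was set for SE change by ANOVA, and no power is stated for incident myopia. Some contrasts, atropine versus control above all, have little power to spare.

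**Working it through.** **The plan's own figure.** There is none for incident myopia or time to onset. The only calculation is for SE change: 174 evaluable children (58 per group), and 58/0.75 = 77.3, rounded up to 78 per group, 234 in all. The dropout step reproduces. The 174 does not: the planning means give f = 0.1554/0.6 = 0.259, which needs 147 (SD 0.65 gives 174). That is a separate matter and does not bear on this point.

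**Inputs from the article.** Yearly SE changes -0.55 (control), -0.17 (DIMS) and -0.38 D (atropine); SD 0.6 D; eight strata; blocks of 3; N = 234 with 25% dropout; event SE ≤ -0.5 D; two-sided 5%.

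**Assumptions, because the article does not give them.** The distribution of baseline SE within its range, the scaling from 12 to 18 months, and the correlation between a child's baseline SE and later shift (zero unless stated). An asymptotic score test stands in for the exact Farrington-Manning test, which is at least as conservative.

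**Step 1, size by formula.** With equal-sized SE strata and event proportions pL and pH in the low-SE and high-SE strata, p = (pL + pH)/2:

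R = {[pL(1 - pL) + pH(1 - pH)]/2} / [p(1 - p)], true size = 2[1 - Φ(1.96/√R)].

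In simulation the planning means and SD 0.6 per year give 18-month control incidences of about 66% and 34%. Then p = 0.50, R = 0.2244/0.25 = 0.898, 1.96/√0.898 = 2.07, and size = 3.9%. Other assumed pairs:

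| Low-SE / high-SE incidence | R | True size |
|---|---|---|
| 30% / 30% | 1.000 | 5.0% |
| 35% / 20% | 0.972 | 4.7% |
| 45% / 15% | 0.893 | 3.8% |
| 60% / 15% | 0.784 | 2.7% |

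**Step 2, size by simulation of the actual design.** At the planning SD: unadjusted score 4.1%, unstratified log-rank 3.7%; Mantel-Haenszel by the randomisation strata 4.9%, stratified log-rank 5.0%. A second set of runs, with baseline SE uniform in its range, gave 4.0 to 4.8% for the score test and 4.2 to 5.2% for Mantel-Haenszel by SE stratum alone.

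**Step 3, power.** MH is Mantel-Haenszel, by the randomisation strata in row 1 and by SE stratum elsewhere. The last column is a logistic test with continuous baseline SE.

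| Scenario (correlation 0) | Contrast | Unadjusted | MH | Logistic |
|---|---|---|---|---|
| Linear yearly shift over 18 months, SD 0.6/year | DIMS vs control | 66% | 70% | 73% |
| 1-year shifts, SD 0.6 | DIMS vs control | 60% | 64% | – |
| Shifts × 1.5, SD 0.6 | Atropine vs control | 34% | 38% | – |
| Shifts × 1.5, SD 0.9 | DIMS vs control | 70.0% | 72.2% | 74.4% |
| Shifts × 1.5, SD 0.9 | Atropine vs control | 20.4% | 21.0% | 22.1% |

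In the first scenario the log-rank test for DIMS versus control goes from 74% to 77% when stratified.

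**Step 4, what the answer turns on.** The correlation between baseline SE and shift was varied. At -0.4 (children starting higher shift more) baseline SE loses its prognostic weight over the period: the unadjusted size is 5.0% and power is 48.9% against 49.0% with Mantel-Haenszel. At +0.4 the gain is about 8 to 11 points; in one case power goes from 20.6% to 32.0%.

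**The case against.** The strongest reply is that the plan states nothing invalid. An unadjusted risk difference with an exact interval and a plain log-rank test are standard, and here they err on the safe side. The outcomes are secondary and exploratory, the primary outcome already has a GEE with baseline SE, and an article may leave covariate lists to a fuller plan. Most of this stands. It limits the point to efficiency, but does not remove it: the article itself names the two tests, and itself writes the adjustment out for SE and axial length only.

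A reader might infer more than the document supports, in three ways.

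- **That every analysis of myopia onset leaves baseline SE out.** The Cox model is described only as handling a time-varying covariate, with no list of fixed covariates. An unstated list is not an exclusion. Whatever that model contains, it does not change the two named tests.
- **That the tests are wrong or could mislead towards a positive finding.** Their error rate is below 5%, not above it.
- **That the loss is reliably 5 points or more.** Gains of that size, such as 59% to 67% for DIMS versus control, come from a logistic likelihood-ratio test that rejects in 5.1 to 5.9% of null trials, so part of the gain is excess size. They also assume zero correlation between baseline SE and shift. The 18-month versions scale the means by 1.5 while keeping the SD at 0.6 or 0.735, whereas a linear shift per child would scale it to 0.9. With that SD the Mantel-Haenszel gain is about 1 to 2 points.

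**Conclusion.** The point holds as a modest loss of efficiency. The Farrington-Manning difference and the log-rank test, as named, do not use factors that the trial stratifies on and itself calls prognostic.

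Under the planning SD of 0.6 D their true size is about 4% instead of 5%. The power given up is roughly 1 to 5 points against Mantel-Haenszel by baseline-SE stratum, and somewhat more against continuous baseline SE. The range is from nothing to about 10 points, and it is driven by a correlation that the article does not report. The figures also rest on an assumed baseline SE distribution, an assumed 18-month scaling and an asymptotic stand-in for the exact test. The direction is secure wherever baseline SE predicts onset within the trial, as the Introduction says it does.

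The outcomes affected are secondary and exploratory. The primary analysis is untouched.

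**What to change.** In the Statistical analysis section, before outcome data are seen:

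1. For incident myopia, report a Mantel-Haenszel risk difference and test stratified by the two-level baseline-SE factor, or a risk difference standardised from a model with treatment, continuous baseline SE, gender and number of myopic parents.
2. Stratify the log-rank test by the baseline-SE stratum.
3. Name baseline SE, gender and parental myopia as covariates in the Cox model, beside whatever time-varying covariate is meant.
4. Keep the unadjusted Farrington-Manning difference as a supportive result.

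The cost is wording only: the factors are known before randomisation and the GEE already uses them. Stratifying on SE alone avoids thin cells; all eight strata would leave on average 174/8/3, about 7 evaluable children, per arm and stratum. There is a small downside: the exact interval becomes supportive, and the standardised estimate, if chosen, depends on a model.

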### Sample size calculation

According to previously randomized clinical trials, the 1-year mean change of cycloplegic SE with the DIMS spectacles, 0.01% atropine eyedrops, and the control group (single vision spectacles or placebo eyedrops) was -0.17 D, -0.38 D and -0.55 D, respectively [25]. The standard deviation (SD) of mean SE changes was around 0.5 to 0.7 in the abovementioned groups, so we choose 0.6 as the SD factor. To achieve 80% power, a significance level of 0.05, 95% CI; two-sided), and 1:1:1 allocation in a test of analysis of variance (ANOVA), the estimated sample size would be 174 participants (58 in each group) based on the calculation using the software G*Power 3.1. With the estimated dropout rate of 25% over the 1.5-year follow-up, a final sample size is 234 participants (78 in each group).

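### The difference in cumulative incidence of myopia is planned as a simple difference of proportions, although 25% dropout is expected and children who leave non-myopic have no month-18 status

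*Protocol article*

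**What the plan says.** The outcome sections rank incident myopia as one of three secondary outcomes and describe it as a cumulative percentage. The follow-up schedule has six visits after baseline, at months 3, 6, 9, 12, 15 and 18, with cycloplegic refraction at each.

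Under Statistical analysis, the between-group comparison uses an exact unconditional method based on the Farrington-Manning score statistic: "we will calculate the difference in the cumulative incidence of myopia among groups of different treatment assignment". On the analysis population: "The analyses on the secondary outcomes will also be conducted with intent-to-treat principles". For the primary outcome, the same section gives intention to treat as its answer to loss to follow-up. The one missing-data method it names, GEE, is tied to the repeated-measures analysis.

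Two analyses that can handle censoring are also planned. One is a time-dependent Cox regression of incidence, described as serving time-varying covariates. The other is Kaplan-Meier with a log-rank test for time to onset, ranked as exploratory.

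The sample size section expects substantial loss: "With the estimated dropout rate of 25% over the 1.5-year follow-up, a final sample size is 234 participants (78 in each group").

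**The concern.** Incident myopia accrues over six visits. A child seen to be myopic at month 6 who then leaves has a known result. A child who leaves at month 6 still non-myopic does not. A binomial comparison has no place for that second child: the child is counted as myopia-free, dropped, or given a value by some rule. Intention to treat settles which arm a child belongs to. It does not supply the missing result.

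Taken at face value, intention to treat with a simple proportion means that all randomised children form the denominator, so children who leave non-myopic count as successes. The arm with more withdrawal then looks better. The arms are nightly drops, spectacles and usual care. They differ visibly, different adverse events are anticipated in the two treated arms, and only those two have a week-2 visit. Unequal withdrawal is therefore plausible, though the document does not predict it. The secondary incidence difference and the exploratory Kaplan-Meier curves could then disagree about the same events solely because of how leavers are handled.

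**Working it through.** **Inputs from the document.** 78 children per arm, 25% dropout over 18 months, six 3-monthly visits. The plan's own inflation reproduces: 58 / 0.75 = 77.3, rounded up to 78 per arm, and 3 × 78 = 234. Expected leavers are 0.25 × 78 = 19.5 per arm.

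**Assumptions (not in the document).** The document gives no 18-month incidence and no dropout by arm. I take true incidence p from 20% to 50%, arm dropout d of 15%, 25% or 35%, a constant onset hazard per visit, and dropout independent of onset, acting before each visit.

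**Formulas.**
- Onset hazard per visit: h = 1 − (1 − p)^(1/6)
- Dropout per interval: q = 1 − (1 − d)^(1/6)
- Probability of remaining in follow-up and non-myopic through one interval: r = (1 − q)(1 − h)
- Observed onsets: E = (1 − q) h (1 − r^6) / (1 − r)
- Followed to month 18 and non-myopic: S = (1 − d)(1 − p)
- All-randomised proportion: E. Known-status proportion (observed onsets plus non-myopic completers): E / (E + S)

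**Example, p = 40%, d = 25%.** h = 0.0816, q = 0.0468, r = 0.8754, S = 0.75 × 0.60 = 0.45. E = 0.9532 × 0.0816 × 0.55 / 0.1246 = 0.343. Known status: 0.343 / 0.793 = 0.433. The share leaving non-myopic is 1 − 0.343 − 0.450 = 0.207, or about 16 of 78 children.

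**True incidence 40%, by dropout.**

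| Dropout | All randomised | Known status |
|---|---|---|
| 15% | 36.7% | 41.8% |
| 25% | 34.3% | 43.3% |
| 35% | 31.9% | 45.0% |

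**True difference of 15 points (40% control, 25% treated).**

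| Dropout control / treated | All randomised | Known status |
|---|---|---|
| 25% / 25% | 13.0 | 15.8 |
| 15% / 35% | 16.9 | 13.0 |
| 35% / 15% | 9.1 | 18.6 |

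**No true difference; dropout 15% in one arm, 35% in the other.** Entries are the 15% arm minus the 35% arm, in points.

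| True incidence | All randomised | Known status |
|---|---|---|
| 20% | +2.5 | −2.1 |
| 30% | +3.6 | −2.8 |
| 40% | +4.8 | −3.2 |
| 50% | +5.8 | −3.3 |

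**Against sampling error.** At 40%, the standard error of the all-randomised difference is √(0.367 × 0.633 / 78 + 0.319 × 0.681 / 78) = 7.6 points, so 4.8 points is about 0.6 of a standard error.

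**Alternatives.** I simulated two arms of 78 with 40% incidence in both and dropout of 35% and 15%. The month-18 Kaplan-Meier difference and the completers-only difference both averaged about zero, with standard deviations of 8.7 and 9.2 points. Kaplan-Meier is therefore unbiased here and somewhat more precise.

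**The case against.** The strongest reply has four parts.

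- **Censoring is already handled.** Both the Cox regression of incidence, at secondary level, and the exploratory Kaplan-Meier analysis can censor a child at the last visit. A reader might infer that the plan has no means of dealing with withdrawn children; the document does not support that. What remains is that Cox gives a hazard ratio and is described as covariate control, while Kaplan-Meier is kept for time to onset. Neither is assigned to the absolute difference.
- **The denominator may be set elsewhere.** An article can leave the counting rule, or imputation, to an analysis plan that is not shown. This stands as far as the bare rule goes, and its absence is not the point made here. The article does fix the estimator, and that estimator cannot use partial follow-up.
- **Distortion is not certain.** A month-18 completers denominator is unbiased when dropout is independent of onset. That is correct, but it discards onsets seen before withdrawal and does not fit the stated intention to treat. With equal dropout and no true effect, no false difference arises under either denominator.
- **The size rests on assumptions.** Incidence and dropout imbalance are assumed, and even a 20-point imbalance gives at most about 0.6 of a standard error at 40% incidence. This stands and limits the weight of the point.

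A reader might also treat this as the trial's key endpoint. The document makes change in cycloplegic refraction primary and bases the sample size on it.

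**Conclusion.** The point holds in a limited form. The protocol fixes a complete-data estimator for a secondary outcome that it expects to be censored, and it relies on a principle that does not supply the missing results. Under an all-randomised reading with equal 25% dropout, the effect is modest: about 34% reported for a true 40%, and about 13 points for a true 15. Under an assumed 15% versus 35% imbalance, a false difference of about 2.5 to 6 points can appear over incidences of 20% to 50%. It reverses to about 2 to 3 points if only known-status children are counted. These figures rest on a constant hazard and dropout independent of onset.

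It would go too far to say that the endpoint will be distorted or that the trial's main conclusion is at risk. The primary outcome is untouched, and the bias depends on which denominator is used and on how dropout falls across arms. The change is still worth making, because the visits and the method are already in the plan.

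**What to change.** In the secondary-outcome paragraph of Statistical analysis:

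- Make the between-arm difference in month-18 cumulative incidence, estimated by Kaplan-Meier over the scheduled visits (or by an interval-censored method, since onset is seen only every three months), the main estimate. Give Greenwood-based intervals.
- Keep all randomised children in their assigned arms and censor those who withdraw non-myopic at their last cycloplegic refraction.
- Keep the Farrington-Manning comparison as supportive, with its denominator stated.
- Add a simple sensitivity analysis in which leavers have a higher or lower risk of onset than those who stay, allowed to differ by arm.

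The cost is wording only: no visit, measurement or software method is added beyond what is planned. The downside is that the interval is no longer exact. The estimate also still assumes that withdrawal is unrelated to onset, which is why the sensitivity analysis is needed.
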